# An ICF-based interdisciplinary case management improves functioning, participation, and well-being for people with disabilities in community rehabilitation: a protocol for a randomised controlled trial

**DOI:** 10.3389/fresc.2026.1745671

**Published:** 2026-03-17

**Keywords:** case management, community-based rehabilitation, interdisciplinary collaboration, international classification of functioning disability and health, people with disabilities, person-centred care, randomised control trial, social participation

## Abstract

**Background:**

Community-delivered rehabilitation (CDR) aims to empower people with disabilities and promote their social inclusion. However, conventional multidisciplinary approaches often lack integration and personalised coordination. The International Classification of Functioning, Disability and Health (ICF) offers a structured framework that facilitates interdisciplinary collaboration, case management and person-centred care. This trial aims to evaluate the effectiveness of an ICF-based interdisciplinary case management model in improving functioning, participation, and subjective well-being among adults with physical disabilities receiving home-based community rehabilitation, compared with usual multidisciplinary care.

**Methods:**

This is a six-month, single-blind, randomised controlled trial. Sixty participants will be recruited and randomly assigned via block randomisation to either an intervention group receiving structured ICF-based interdisciplinary case management or a control group receiving usual multidisciplinary care. The inclusion criteria were adults with physical disabilities eligible for CDR; exclusion criteria included severe cognitive impairment or inability to provide informed consent. The intervention consists of ICF-based assessments using the ICF Rehabilitation Set and Minimal Set of Environmental Factors, collaborative goal setting, monthly interdisciplinary case conferences, and coordinated care planning. The primary outcomes are functioning (WHO Disability Assessment Schedule 2.0, 36-item version) and well-being (Satisfaction with Life Scale). The secondary outcomes are changes in ICF qualifiers and therapist-related clinical outcomes (Australian Therapy Outcome Measures). Outcomes will be assessed at baseline and six months. Data will be analysed via intention-to-treat principles and generalised linear mixed models (GLMMs). Recruitment began in May 2025 and is expected to be completed by December 2025, with follow-up concluded by July 2026.

**Discussion:**

This trial will generate empirical evidence on the use of the ICF as a framework for structured interdisciplinary case management in CDR. The findings may inform service planning, interprofessional training, and policy development to promote holistic, person-centred disability care.

**Clinical Trial Registration:**
https://www.chictr.org.cn/hvshowprojectEN.html?id=284308&v=1.0.

## Introduction

1

Many people with disabilities (PWDs) face significant challenges in regaining independence, social participation and quality of life. The challenges are imposed not only by the limitations in physical capacity, but also by family members overprotecting individuals with disabilities by performing tasks for them, inadvertently limiting their autonomy, or societal attitudes may exclude them due to physical or social discrimination. Community-based rehabilitation (CBR) represents a paradigm shift in healthcare, prioritising the empowerment of PWD and fostering their social inclusion within their own community (1). Because it is implemented in more than 90 countries worldwide, CBR has arisen as a holistic approach to address the above challenges by enabling PWD to fully participate in the community (2, 3). The role of CBR is to empower PWD and their families by promoting, supporting and facilitating their active involvement in issues that affect their lives (4, 5).

Over the past four decades, the concept of CBR has evolved substantially. Originally introduced by the World Health Organization (WHO) in 1976 as a strategy to deliver rehabilitation services at community level, CBR initially focused on providing basic rehabilitation techniques in resource-limited settings (6). However, the conceptual framework of CBR has shifted towards a broader rights-based, multisectoral approach known as community-based inclusive development (CBID), which emphasises empowerment, advocacy, social inclusion, and equalisation of opportunities rather than direct service provision. Within this evolution, health-related rehabilitation delivered in community settings is more appropriately described as community-delivered rehabilitation (CDR), integrated within the health system and complementing institution-based services.

The International Classification of Functioning, Disability, and Health (ICF), developed by the WHO in 2001, offers a biopsychosocial model that integrates medical and social perspectives on health and disability. Unlike the traditional medical model, which focuses primarily on impairments, the ICF framework emphasises the functioning of a person across different components, including body functions, body structures, activities and participation, and contextual factors. The latter includes environmental facilitators, barriers and personal characteristics, thereby integrating medical and social dimensions of disability (7). It considers the interaction between the health conditions of PWD and the contextual factors that influence how PWD function and participate in their community, which, in turn, promotes a scientific understanding of functioning and disability. This comprehensive framework aligns with the principle of CDR, which aims to enable PWD to achieve and maintain optimal functioning by addressing the medical, psychosocial, economic and environmental aspects of rehabilitation.

It has been proposed that an interdisciplinary approach designed to optimise functioning in various domains provides benefits to PWD (8). Traditional multidisciplinary approaches, where different professionals work in parallel with limited integration of their interventions, often suffer from fragmentation and a lack of seamless coordination, potentially hindering the delivery of truly person-centred care (9). Interdisciplinary case management is a more personalised approach where different professionals collaborate with service users to assess their needs, set rehabilitation goals and ensure that the care is cohesive, goal-oriented and aligned with the unique functional and contextual needs (10, 11).

The ICF provides a framework and common language to promote interdisciplinary collaboration. Studies have demonstrated that ICF application enhances care coordination and interdisciplinary collaboration and provides a common language for describing and addressing disability (12, 13). Furthermore, an ICF-based assessment and intervention planning model specifically for community rehabilitation settings has been proposed, incorporating structured prioritisation mechanisms to guide case management in complex community contexts (6). Integrating the ICF into case management can enhance interprofessional learning by promoting a multidimensional perspective of an individual's health concerns (14, 15).

However, the focus on studying the clinical outcomes of the application of the ICF framework in interdisciplinary case management, particularly for individuals with physical disabilities, remains underexplored. Emerging research has shown that the clinical application of the ICF model in stroke survivors, including the use of the ICF core set in the assessment and goal setting, by a single rehabilitation discipline such as physiotherapy and occupational therapy, can improve patient outcomes (16, 17). Recently, Wong et al. (18) investigated an 8–12-week community-based multidisciplinary rehabilitation programme for poststroke patients in Hong Kong. The multidisciplinary team, composed of physiotherapists, occupational therapists and speech therapists, was responsible for offering different modules in ICF activities and participation domains. Each of the disciplines set goals and developed training content, emphasising resuming life roles and community reintegration. They revealed that the participants in their study showed significant improvements in all aspects of body functions, activities and participation, which also predict patients' satisfaction. The above studies suggest that the clinical application of ICF by a single professional or a multidisciplinary team could improve clinical outcomes. Studies have also suggested that an interdisciplinary team approach in rehabilitation could enhance teamwork and team effectiveness (19) and promote clinical outcomes (20) compared with usual care.

Therefore, it is reasonable to hypothesise that applying the ICF model in an interdisciplinary rehabilitation programme would be even more effective than a traditional multidisciplinary rehabilitation programme in enhancing functioning and facilitating community reintegration holistically in PWD, as an interdisciplinary approach allows for the integration of complementary expertise from different professionals to address the multifaceted needs of PWD. ICF-based approaches can further enhance interdisciplinary communication and reduce duplication of efforts among rehabilitation professionals, which in turn improves cost-effectiveness (21). Usual multidisciplinary care provides a relevant and pragmatic comparator, reflecting current community rehabilitation service structures. This allows us to evaluate the added value of an ICF-based Interdisciplinary case management (ICFIDCM) model, which is hypothesised to offer more coordinated, goal-oriented, and integrated care, potentially better addressing the complex, interactional needs of PWD (22).

Despite the theoretical and practical alignment between CDR and the ICF, several important gaps remain in both evidence and practice within the broader CBR literature. Many CBR programmes continue to focus predominantly on impairments and activity limitations, often giving less systematic attention to participation and the contextual factors that are central to the ICF model (5, 12, 23). This limited integration restricts the ability of CBR to fully realise its potential in promoting holistic, person-centred outcomes for PWD (13, 24).

Additionally, the application of the ICF framework in CDR programs varies widely across programs in regard to assessment, goal setting, and outcome evaluation (25, 26). The inconsistent application of ICF-based approaches across different settings creates difficulties when trying to compare results between locations and establish general findings about ICF-based intervention success (18). Another persistent gap is the underutilisation of interdisciplinary case management in community settings. While the benefits of interdisciplinary collaboration are well recognised in the literature (19, 27), including improved outcomes and cost-effectiveness in community-based interventions (20), practical implementation remains limited, often due to resource constraints, a lack of training, and systemic barriers (28).

In addition, while different core sets, e.g., the ICF Rehabilitation Set and Minimal Set of Environmental Factors, were developed originally for clinical use, their application is increasingly extending into broader statistical and monitoring contexts (29, 30). The absence of research on core set implementation in interdisciplinary case management for community rehabilitation requires studies that assess both clinical results, practicality, and usefulness of these tools for standardised care coordination (31, 32).

Perhaps most critically, the current research on ICF-based interventions in CDR relies mainly on observational and quasi-experimental studies (16, 18, 23, 33). This means that the current literature lacks sufficient high-quality randomised controlled trials (RCTs) that study the effects of structured ICFIDCM models on functioning, participation, and well-being in actual community settings (34).

The present study design aims to address the above knowledge gaps that exist in current evidence. It evaluates an ICFIDCM model within CDR services to measure its effects on the functioning, participation, and well-being of PWD. It uses ICF-based assessment tools and collaborative goal setting to deliver person-centred care while evaluating ICFIDCM against traditional multidisciplinary care. In doing so, this research aims to establish strong evidence that will help develop optimal CDR practices.

## Methods and analysis

2

### Research aim

2.1

The trial aims to evaluate the effectiveness of the ICFIDCM compared with that of usual multidisciplinary care in improving the functioning and well-being of people with disabilities who receive home-based community rehabilitation. Two primary outcome indicators, which are both patient-reported outcomes (PROs), are functioning (World Health Organization Disability Assessment Schedule 2.0, WHODAS 2.0, 36-item version) and well-being (Satisfaction with Life Scale, SWLS). Two secondary outcome indicators, therapist-reported outcomes (TROs), are changes in ICF qualifiers and Australian Therapy Outcome Measures (AusTOMs). We hypothesised that, compared with the usual care control group, participants receiving the ICFIDCM would demonstrate greater improvements from baseline to six months in terms of functioning (lower WHODAS 2.0 scores) and subjective well-being (higher SWLS scores). For the secondary outcome, compared with the control group, we expect to see greater pre-post improvements in therapist-rated functioning (improved ICF qualifier scores) and in therapist-rated clinical outcomes (higher AusTOMs scores) among participants in the intervention group.

### Trial design

2.2

A six-month parallel group randomised controlled trial (RCT) will be conducted. PWDs newly referred to and eligible for the Home Care Service for Persons with Severe Disabilities (HCS), which provides home-based rehabilitation services, will be recruited. After providing informed consent and completing baseline assessments, participants will be randomly allocated to either the treatment group (ICFIDCM) or the control group (usual multidisciplinary case management). This study was registered with the Chinese Clinical Trial Registry (https://www.chictr.org.cn): (ChiCTR2500109152) and approved by the Research Ethics Committee of Hong Kong Metropolitan University (HE-SF2025/27). The study protocols followed the SPIRIT guidelines.

#### Participants

2.2.1

##### Inclusion criteria

2.2.1.1

Adults aged ≥18 years with diagnosed physical disabilities who are newly referred to and eligible for HCS, who are medically stable, and who are able to provide written consent.

##### Exclusion criteria

2.2.1.2

Individuals with acute or unstable medical conditions requiring hospitalisation, terminal illnesses with a prognosis of less than six months, psychological disorders or severe mental illness.

Individuals with severe cognitive impairments, e.g., those diagnosed with severe dementia, intellectual disability, or other conditions preventing meaningful participation in the study.

### Sample size determination

2.3

The primary outcomes of this study are PROs of functioning and well-being (WHODAS 2.0 and SWLS). We identified Hussain et al. (2025), who reported a between-group effect size of d = 0.8 on WHODAS 2.0 scores at the 20-week follow-up in a community-based, culturally adapted problem management intervention trial for people with disability (35). We use this study to inform our sample size calculation since the follow-up duration and outcome measure closely align with our six-month endpoint. Although Hussain et al. (2025) used the 12-item WHODAS 2.0 version, psychometric studies have demonstrated high concordance between the 12- and 36-item versions (correlation coefficients of *r* ≥ 0.915 between total scores on these two versions). This strong agreement supports the application of an effect size derived from the 12-item version to the 36-item WHODAS 2.0.

Using G*Power (G*Power 3, version 3.1.9.6) (36), with a α level of 0.05 (two-tailed), a power of 0.80, and an effect size of 0.8 as reported, a minimum sample size of approximately 26 participants per group (a total of 52 participants) was determined. Assuming a 15% attrition rate (18), the study will recruit a total of 60 participants who are PWD, newly referred and eligible service users of home care services. Considering that approximately 120–160 new case referrals are received per year, recruitment will take a minimum of 6 months.

### Recruitment and consent procedures

2.4

Participants will be recruited from HCS operated by the Yang Memorial Methodist Social Service (YMMSS). New service users are identified through the service referral system. Trained social workers (case managers) approach potential participants, explain the study and obtain written informed consent at the participant's home. Written informed consent will be stored safely in the main office of the home care service teams.

Participants may withdraw from the study at any point without consequences. Dropouts will be recorded if a participant (a) withdraws consent or (b) dies before the follow-up assessment. Withdrawn cases will remain in the intention-to-treat analysis using their most recent available data. No dropout cases will be recruited.

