### Outcome measures

2.9

All participants will be assessed at baseline (preintervention) and after six months (postintervention) via the following assessment tools.

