## Data analysis

3

Data analysis will begin only after the follow-up stage. The PI and SI will have access to the final trial dataset. The quantitative data will be analysed via SPSS Statistics 27.0 (IBM). Data cleaning will include systematic screening for outliers and any inconsistencies in the data. Multiple imputations will be considered for missing data. Descriptive statistics will be applied as appropriate for all variables.

**Primary outcomes.** To determine whether functioning (WHODAS 2.0) and subjective well-being (SWLS) improve following the implementation of the ICFIDCM, we will compare intervention and control groups via generalised linear mixed models (GLMMs). Fixed effects will include time (baseline, 6 months), study group, and the group × time interaction, with participant ID as a random effect to account for repeated measures. The target test statistic will be the mean difference (with 95% confidence intervals), estimated via maximum likelihood methods. Two-sided significance will be set at 0.05. **Secondary outcomes.** To analyse the target secondary outcomes (ICF qualifiers and AusTOMs) over the course of time, descriptive analyses will first summarise change scores over time. Subsequently, GLMMs will be used to estimate group differences in changes, with the same fixed- and random-effects structure as above. The results will be expressed as estimated marginal means with 95% confidence intervals.

Treatment dosage variables (e.g., number of visits, total contact time) will be recorded and included as covariates in exploratory sensitivity analyses to assess their potential influence on treatment effects. Although the study is not powered for formal subgroup comparisons, exploratory sensitivity analyses will be performed to examine potential effect modification. Specifically, interaction terms between group allocation and age group, primary diagnosis, and treatment dosage will be examined within the mixed-effects model framework. These analyses are exploratory in nature and will be interpreted cautiously given the limited sample size.

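### Section 2.4's rule for withdrawn cases most naturally reads as baseline carried forward, and it is not reconciled with the likelihood-based model in Section 3

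*Protocol article*

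**What the plan says.** Section 2.4 (Recruitment and consent procedures) defines dropout: "Dropouts will be recorded if a participant (a) withdraws consent or (b) dies before the follow-up assessment". The next sentence gives the rule: "Withdrawn cases will remain in the intention-to-treat analysis using their most recent available data".

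Section 2.9 (Outcome measures) sets two assessment times: "All participants will be assessed at baseline (preintervention) and after six months (postintervention) via the following assessment tools". The abstract agrees: "Outcomes will be assessed at baseline and six months". The article describes no outcome assessment at the time of withdrawal.

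Section 3 (Data analysis) sets out the primary model: "Fixed effects will include time (baseline, 6 months), study group, and the group × time interaction, with participant ID as a random effect". The mean difference is to be estimated by maximum likelihood. On missing values it says: "Multiple imputations will be considered for missing data". Section 3 does not mention carrying values forward, and neither section refers to the other.

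**The concern.** With one baseline and one follow-up visit, the most recent score of anyone who leaves before six months is the baseline score. Using it as that person's outcome enters a change of exactly zero and treats it as observed.

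The methods in Section 3 do something else. A maximum-likelihood mixed model uses the rows that exist and leaves the missing six-month row missing. Multiple imputation draws several plausible values. Neither fixes change at zero. An analyst following Section 2.4 and one following Section 3 could therefore report different primary results from the same data.

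Two things are at stake. One is dilution of a real effect on both primary outcomes, in a trial enlarged from 52 to 60 specifically to absorb attrition. The other is a choice of method left open until the data have been seen.

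**Working it through.** **Inputs from the protocol (Sections 2.3 and 2.5).** Effect size d = 0.8, two-sided alpha 0.05, power 0.80, 26 per group (52 in total), 15% attrition, 60 recruited, 1:1 allocation, hence 30 per arm.

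**Inputs assumed, because the article does not give them.** Correlation between baseline and follow-up 0.5, so the SD of change equals the SD of a single score: √(2 × (1 − 0.5)) = 1. Control-arm improvement c of 0 to 0.5 SD. Dropout rates by arm. Dropout completely at random.

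**1. The plan's own figure.** A two-sample t-test with d = 0.8 needs 26 per group (power 0.807), as stated. For attrition, 52 × 1.15 = 59.8, which gives the stated 60; 52 / 0.85 = 61.2 gives 62. The difference of two participants is immaterial here. With 15% lost, 60 × 0.85 = 51 remain, about 25.5 per arm, and power is 0.80. The planned sample therefore nearly delivers its target if observed scores are analysed.

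**2. Expected estimate under carry-forward.** Let dT and dC be the dropout rates in the intervention and control arms.

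Expected difference in change = (1 − dT)(c + 0.8) − (1 − dC)c

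| Dropout, intervention / control | c (SD) | Estimate if true effect is 0.8 SD | Estimate if there is no effect |
|---|---|---|---|
| 15% / 15% | any | 0.85 × 0.8 = 0.68 | 0 |
| 20% / 10% | 0.3 | 0.80 × 1.1 − 0.90 × 0.3 = 0.61 | −0.03 |
| 10% / 20% | 0.3 | 0.90 × 1.1 − 0.80 × 0.3 = 0.75 | +0.03 |
| 20% / 10% | 0.5 | 0.80 × 1.3 − 0.90 × 0.5 = 0.59 | −0.05 |
| 10% / 20% | 0.5 | 0.90 × 1.3 − 0.80 × 0.5 = 0.77 | +0.05 |
| 0% / 30% | 0.5 | 1.3 − 0.70 × 0.5 = 0.95 | +0.15 |

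Only the first row uses the protocol's rate alone. The others show direction and rough size under assumed rates.

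**3. Power at 15% / 15%, 30 per arm.** Putting d = 0.68 straight into the t-test gives 0.74. The zeros also alter the variance of change, which in an arm with mean change m becomes 0.85 × 1 + 0.15 × 0.85 × m².

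- c = 0.3: 0.85 + 0.1275 × 1.1² = 1.004 and 0.85 + 0.1275 × 0.3² = 0.861. The average is 0.933 and the SD 0.966, so the standardised effect is 0.68 / 0.966 = 0.70 and power about 0.76. Simulation (10,000 runs) gave 0.77.
- c = 0.5: variances 1.065 and 0.882, SD 0.987, standardised effect 0.69, power about 0.75. Simulation (6,000 runs) gave 0.74 to 0.75.

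The comparator in the simulations was change scores from observed follow-ups only, which should be close to the likelihood model with two visits. It gave an estimate of 0.80 SD, power of about 0.79 to 0.80 and 95% interval coverage of 0.95. Coverage under carry-forward at 15% / 15% was 0.92.

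**4. Type I error.** With no true effect and c = 0.5, carry-forward gave 0.050 at 15% / 15%, 0.052 at 10% / 20%, and 0.099 at 0% / 30%.

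**5. Sensitivity to the correlation.** At 0.7 instead of 0.5 (c = 0.3, 15% / 15%), power was 0.92 with carry-forward and 0.95 with observed scores. The attenuation to 0.68 SD was unchanged.

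**The case against.** The strongest reply is that Section 2.4 never says a value is carried forward, that a six-month score is filled in, or that change is set to zero. It may mean only that a withdrawn participant is kept and contributes whatever scores exist, which a maximum-likelihood mixed model does with a baseline-only record. Section 3, not the recruitment section, sets the estimation method. This stands as a possible reading. However, specifying the most recent data points to one value chosen to serve as the outcome, and a reader cannot tell which meaning was intended. Either way the sentence needs the same correction.

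A reader might infer that the two sections flatly contradict each other. The documents do not support that. Multiple imputation is only to be considered, so Section 3 fixes no imputation rule for Section 2.4 to break. What exists is two unreconciled statements about the same missing values.

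A reader might also infer that the protocol expressly assigns six-month scores to participants who died. It does not. The rule names withdrawn cases; deaths come in only because the preceding sentence counts anyone who "dies before the follow-up assessment" as a dropout. The inference is natural, but it is an inference.

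Finally, it is tempting to say that the rule manufactures a false positive result. At equal dropout it does not. A type I error near 0.10 appeared only at 0% versus 30% dropout, which nothing in the article suggests. The shortfall in coverage at equal dropout comes from the attenuated estimate: with no true effect, coverage was 0.95.

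**Conclusion.** The point holds as one of unclear and unreconciled wording whose most natural reading is harmful. This should be fixed; it does not invalidate the design.

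Read as carry-forward, the rule shrinks a true effect by the dropout rate when dropout is equal: 0.80 to 0.68 SD at 15%. That result needs only the protocol's rate, dropout unrelated to outcome, and dropouts who would otherwise have changed as the others do. If dropouts truly did not change, zero would be correct for them. The power loss, from about 0.79–0.80 to about 0.74–0.77, also rests on the assumed correlation of 0.5. At 0.7 power falls too but stays above 0.80. Direction and size under unequal dropout depend wholly on assumed arm-specific rates and shared change, and should be taken as illustration.

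**What to change.** In Section 2.4, delete the closing phrase about most recent data. State in both Section 2.4 and Section 3 that all randomised participants enter the likelihood-based mixed model with the scores actually observed, and that no baseline value is substituted for a missing six-month score. Make clear that this also applies to participants who die before follow-up, since Section 2.4 counts them as dropouts. The likelihood analysis relies on values being missing at random, and the text should say so.

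Multiple imputation may serve as a sensitivity analysis; its details can be left to the SAP.

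The cost is wording in two sections. The model is already planned and no new data are needed. Section 3 says analysis starts only after follow-up, which Section 5.2 expects to end by 31 July 2026, so the change should be recorded before then and not chosen once results are known.
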